### Summary study protocol

PASS is a multicenter prospective, randomized, phase III, open-label, blinded end-point superiority trial (PROBE) of standard care with preventive ceftriaxone treatment compared to standard care without preventive ceftriaxone. Adult patients with stroke (both ischemic and hemorrhagic), a score ≥1 on the National Institutes of Health Stroke Scale (NIHSS) and stroke onset within 24 hours were included
[8]. Patients were excluded in case of infection at admission, use of antibiotics within 24 hours before admission, previous hypersensitivity or anaphylaxis to cephalosporins or penicillin, subarachnoid hemorrhage, pregnancy or when death seemed imminent. Patients were randomly assigned to either ceftriaxone at a dose of 2 g, given every 24 h intravenously for 4 days, in addition to stroke-unit care, or standard stroke-unit care without preventive antibiotic therapy. Randomization was performed through ALEA (online software for randomized trials;
https://nl.tenalea.net/amc/ALEA/Login.aspx) and is based on a uniform distribution; weight of the arms is equal (1:1). Randomization is stratified according to study center (academic hospital, large non-academic hospital, or small non-academic hospital) and stroke severity (score on NIHSS 1 to 9 or >9) and performed by using random blocks with a maximum block size of 6; blocks of 2, 4 and 6 are made per stratum combination

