[9]. The study has a PROBE design, which implies that blinding is lost, but only as to treatment. Patient and physician were aware of treatment allocation; however, the assessors of outcome were not. Data were collected on admission, during hospital stay, and at 3 months by standardized case record forms. The primary outcome is functional outcome at 3 months follow-up, as assessed on the mRS during a structured telephone interview by a trained assessor blinded for treatment allocation. Secondary outcomes are death rate at discharge and at 3 months, infection rate during hospital admission, length of hospital admission, volume of post-stroke care, use of antibiotics during hospital stay, quality adjusted life years (QALYs) and costs. Safety outcomes are complications of treatment, Serious adverse events (SAEs) and suspected unexpected serious adverse reactions (SUSARs). In the initial trial protocol, we presented a binary logistic regression analysis on the dichotomized mRS (0 to 2 versus 3 to 6) as primary outcome, requiring a sample size of 3,200 patients, and a proportional odds model in a secondary analysis of the primary end point
[9]. Blinded for any of the outcomes, we have changed the primary analysis in PASS from a binary logistic to an ordinal logistic regression on the original mRS, enhancing statistical power. The adapted power analysis showed that with identical assumptions on the clinical effect, using a 0.05 two-sided significance level and 80% study power, 2,550 patients were needed
[9]. The analysis of dichotomized mRS data will now be the secondary analysis of the primary end point.

On 23 March 2014, all patients were included and the last follow-up is expected in June 2014. For the complete study protocol and update, we refer to previous publications
[6, 7].

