### Assessment of safety outcomes

Safety outcomes are complications of treatment, SAEs and SUSARs. All SAEs and SUSARs during the hospital stay are recorded in case record forms by the treating physician and reported to the trial office. SAEs and SUSARs occurring after discharge are recorded during the follow-up interview at 3 months. The physician records treatment complications in the CRF (diarrhea caused by *C. difficile*, allergic reaction that caused cessation of ceftriaxone, infection with ceftriaxone resistant microorganism, phlebitis at place of IV-catheter, elevation of liver enzymes, oliguria or elevation of serum creatinine).

Cause of death will be reviewed by two independent observers. They will use information from the hospital discharge letter or the medical correspondence received by the general practitioner in case the patient died after discharge. Discrepancies will be reviewed in a consensus meeting in the presence of a third investigator. Outcome parameters were derived from three recent cardiovascular trials and were modified for expected outcomes in our study
[14–16]. A distinction will be made among a cardiovascular cause (brain infarction, brain hemorrhage, myocardial- or pulmonary embolism. or another cardiovascular cause), an infection (pneumonia, sepsis or another infection), death by any type of malignancy, death by any other cause (for example, traffic accident), withdrawal of treatment due to a poor prognosis or unknown cause of death.

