### Safety outcomes

Complications of treatment, SAE’s and SUSAR’s per patient will be tabulated according to treatment group, and analyzed using the chi-squared test (Table 
5 and table 
6).

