**Table 6 Tab6:** **Complications of treatment**

Adverse reaction - % n/N	Ceftriaxone + standard care (n = …)	Standard care (n = …)	***P***
- Diarrhea caused by *C. difficile*			
- Allergic reaction that caused cessation of ceftriaxone			
- Infection with ceftriaxone-resistant microorganism			
- Phlebitis at place of IV-catheter			
- Elevation of liver enzymes			
- Oliguria or elevation of serum creatinine			

Total number of adverse reactions - number %.

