### Discussion

The aim of our study is to investigate whether preventive antibiotic therapy improves functional outcome by reducing the number of infections in acute stroke patients. With this SAP, we present the analyses that will be published in the primary publication. By publishing the statistical analysis plan before knowledge of any outcome, we stimulate transparency of scientific conduct and allow others to add timely suggestions for additional analyses.

Patients in the acute phase of stroke are at risk for infections. A systematic review and meta-analysis of 87 studies showed that infections complicate stroke in 30% of all stroke patients. Pneumonia was associated with mortality with an OR of 3.62 (95% CI 2.80 to 4.68)
[3]. The effect of preventive antibiotic therapy on outcome in stroke patients has been investigated in few studies. Two meta-analyses of these studies showed that preventive antibiotic therapy reduced the number of infections
[4, 5]. The proportion of patients who died and the number of disabled patients were not significantly reduced, but numbers of included patients were small.

The PROBE design with open-label preventive antibiotics might introduce detection bias for infection. Physicians are aware of the treatment allocation, which potentially influences decisions on nonscheduled treatment (that is, the detection and treatment of patients with infection). This might influence the outcome measure of infection rate. To control for this bias, we will provide a secondary judgement of infection diagnosis by a blinded expert panel, according to CDC criteria. The CDC criteria are restrictive and use ancillary investigations such as blood tests, chest X-rays and culture results to confirm the diagnosis of infection. In clinical practice, for a stroke patient with fever, a cough and abnormalities on auscultation, a physician will often not wait for culture results or refrain from treating pneumonia when a chest X-ray does not (yet) show a consolidation.

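### The planned chi-squared test on SUSARs has no valid comparator, and three Table 6 rows are tested between arms on unblinded entries without a common criterion

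*SAP article*

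**What the plan says.** Assessment of safety outcomes names six treatment complications and says who enters them: "The physician records treatment complications in the CRF". Summary study protocol states that "Patient and physician were aware of treatment allocation; however, the assessors of outcome were not". The comparator in the same section is "or standard stroke-unit care without preventive antibiotic therapy"; no placebo is mentioned.

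The analysis rule under Safety outcomes is: "Complications of treatment, SAE’s and SUSAR’s per patient will be tabulated according to treatment group, and analyzed using the chi-squared test". Table 6 has a ceftriaxone column, a standard-care column and a P column, and its row header is "Adverse reaction - % n/N".

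Two other places matter. Infection rate during hospital admission gives *C. difficile* a case definition (diarrhea with a positive toxin test) and a panel review. The Discussion concedes, for infection, that "Physicians are aware of the treatment allocation, which potentially influences decisions on nonscheduled treatment", and offers a blinded panel in response. It makes no matching statement about the complications in Table 6.

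**The concern.** A between-arm test of harm is informative when an event has the same chance of being counted in either arm if the drug does nothing. Two parts of this plan do not secure that.

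- **SUSARs.** The category contains a suspicion that the study drug caused the event. Patients without study drug cannot contribute, whatever happens to them.
- **Table 6.** The labels *treatment complication* and *adverse reaction* invite a judgement about cause, and the person recording knows who received ceftriaxone. A raised creatinine or liver enzyme can occur in either arm. If it is noted more readily on ceftriaxone, the P value mixes drug toxicity with recording behaviour.

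At stake is the reading of the trial's tested comparison of treatment complications. The primary outcome, mRS by blinded telephone interview, is not affected.

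**Working it through.** The SAP states no figure on this point, so there is none to reproduce. The check is mainly a reading of the rows, followed by an illustration of scale.

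**1. SUSARs.** Safety is analysed per protocol (Definition of intention-to-treat and per-protocol population). That set excludes treatment deviations, and a control is on protocol only if no preventive antibiotic was given. No control in the safety set therefore has study drug, and the control SUSAR count is zero by construction.

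For *x* events against 0 with *n* per arm, the uncorrected statistic reduces to χ² = 2n·x/(2n − x). With 2,550 patients allocated 1:1, n = 1,275 (the per-protocol set will be somewhat smaller):

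- x = 3: 2,550 × 3/2,547 = 3.00, p = 0.083
- x = 4: 2,550 × 4/2,546 = 4.01, p = 0.045

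With continuity correction, χ² = 2n(x − 1)²/[x(2n − x)]. For x = 6 this is 2,550 × 25/(6 × 2,544) = 4.18, p = 0.041. So 4 to 6 SUSARs reach significance although the control count could not have been anything but zero.

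**2. Table 6, row by row, as far as this document goes.**

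| Row | Attribution-free criterion | Review beyond the treating physician |
|---|---|---|
| *C. difficile* diarrhea | yes, case definition | yes, panel |
| Allergic reaction | no; tied to stopping ceftriaxone | none stated |
| Resistant microorganism | describes the organism; needs a culture | partial: the blinded infection panel reviews patients with a clinical diagnosis of infection, but is not said to classify resistance |
| Phlebitis | none stated | none stated |
| Liver enzymes | none stated | none stated |
| Oliguria or creatinine | none stated | none stated |

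The allergy row, "Allergic reaction that caused cessation of ceftriaxone", is drug-specific as worded: a control never given ceftriaxone cannot meet it. The exposed rows are the last three.

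**3. Illustration of scale.** The inputs are assumptions: n = 1,275 per arm, the same true risk *p* in both arms, all ceftriaxone events recorded, a fraction *c* of control events recorded, and two-sided 0.05 (stated in the SAP for the primary analysis only). With recorded control risk q = c·p and m = (p + q)/2:

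Power = Φ{[(p − q) − 1.96·√(2m(1 − m)/n)] / √(p(1 − p)/n + q(1 − q)/n)}

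For p = 5% and c = 0.75: q = 3.75%, the difference is 0.0125, and the two standard errors are 0.00810 and 0.00810. Then (0.0125 − 0.01588)/0.00810 = −0.417, and Φ = 0.338.

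Chance of a significant excess on ceftriaxone when the true risks are equal:

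| True risk | c = 0.90 | c = 0.75 | c = 0.50 |
|---|---|---|---|
| 2% | 5.6% | 15.9% | 54.7% |
| 5% | 8.6% | 33.8% | 91.4% |
| 10% | 13.6% | 60.8% | 99.8% |

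The apparent odds ratio is about 1.1, 1.34 to 1.37, and 2.0 to 2.1 across the columns. With equal recording the two-sided test rejects in 5%, half of it in this direction. Simulation of the same cells, counting rejections in either direction, agrees: for example 16%, 34% and 61% at c = 0.75.

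**The case against.** The strongest reply is that the Table 6 items form a closed checklist, and the phlebitis, liver and renal items carry no relatedness wording. Data came from standardized case record forms, and every row has a count and denominator for standard care. On that reading the umbrella label is loose and the same boxes were completed in both arms. Controls could also have phlebitis at a catheter site, or receive antibiotics for an established infection. The full protocol and the CRF, which are not shown, may hold thresholds or a laboratory schedule.

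Much of this stands. A reader might infer that an event enters Table 6 only if the physician blames the treatment, or that control events were in fact missed. The document supports neither: the first rests on two labels, and the second is stated nowhere. Nor is *C. difficile* the only row with any protection, since resistant infections fall partly within the blinded panel's review. The table of false-positive rates shows what unequal recording would do, not that it happened; at 90% recording the effect is small.

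Two things do not go away. A standard-care column does not fix how events enter it, and this document sets no symmetric rule for the three exposed rows while committing to a P value for each. The SUSAR test is wrong as written whatever the CRF contains. In mitigation, neither Table 5 nor Table 6 has a SUSAR row, so the test appears only in the text.

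**Conclusion.** The point holds in two parts of different strength.

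- **SUSARs: firm.** The between-arm test is uninformative by definition. This needs no assumption about event rates.
- **Phlebitis, liver and renal rows: a risk, not a demonstrated bias.** Unblinded entry, causal labels and the lack of a common criterion or blinded review in this document allow differential recording, which would run against ceftriaxone. Its size is unknown. The illustrated range, from about 6% to nearly 100% false significant excess, rests wholly on assumed risks of 2% to 10% and assumed recording ratios of 0.90 to 0.50.

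The finding does not make every P value in Table 6 unusable, and it does not reach the blinded primary outcome. It is worth correcting because the change is cheap and, with outcomes still blinded, can be fixed in advance.

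**What to change.** 1. **Safety outcomes:** remove SUSARs from the chi-squared sentence and list them descriptively for the ceftriaxone arm, without a between-arm test.
2. **Assessment of safety outcomes and Table 6:** retitle the row header *Event*. State that all rows other than the allergy row are counted in both arms irrespective of suspected relation to treatment, applying one common criterion to CRF results where these were recorded.
3. **Rows with only an unblinded yes/no entry:** report counts and percentages by arm without a P value, and state the open-label ascertainment limit, as the Discussion already does for infection. Decide which rows these are from the CRF design, before the code is broken.

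A second denominator of patients tested, or demoting rows where testing proves unequal, is not advised: the first conditions on a post-randomisation event and the second is a data-dependent choice without a threshold.

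The cost is a few lines of text, one table header and modest programming on recorded results; no new data are needed. Inclusion has closed, so recording itself cannot be redesigned. The downside is that some rows lose a P value.

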### Protocol deviations in eligibility, consent procedure, treatment

When a patient was randomized but did not adhere to inclusion or exclusion criteria, this was considered a protocol deviation regarding eligibility. Patients with protocol deviations in eligibility were included in the ITT analysis, but excluded from PP analysis.In each center, the local investigator obtained written informed consent from the patient or representative according to the PASS study protocol. Patients who withdrew consent directly after randomization were excluded from further analysis. The flow of patients is displayed in the CONSORT flowchart (Figure 
1).

Treatment allocation was regarded as carried out according to the study protocol when a patient randomized for ceftriaxone in addition to standard care received ceftriaxone 2 gram each 24 hours for 4 days. Patients were also considered as treated PP when treatment was terminated within 4 days due to discharge, death, a palliative care policy, an allergic reaction without anaphylaxis or a previous allergic reaction in medical history (see inclusion and exclusion criteria and protocol deviation in eligibility), other side effects of treatment, or when treatment with ceftriaxone was changed into treatment with another antibiotic because of an infection because these situations and what to do were all defined and described in the initial protocol
[6]. In patients allocated to standard care, treatment was carried out according to the study protocol when patients did not receive preventive antibiotic therapy.

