**Table 5 Tab5:** **Number and type of serious adverse events**

Type of SAE* -% n/N	Ceftriaxone + standard care (n = …)	Standard care (n = …)	***P***
- Death			
- Life-threatening event			
- New hospitalization			
- Prolongation of existing hospitalization			
- Persistence of significant disability or incapacity			
Total number of SAE’s			

*SAE, serious adverse event.

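### The only allergy item among the treatment complications requires that ceftriaxone was stopped, so other allergic reactions are left out of that row and of the Table 6 total

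*SAP article*

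**What the plan says.** Under Assessment of safety outcomes, the SAP article lists the treatment complications that the physician records in the CRF. Allergy enters that list only as "allergic reaction that caused cessation of ceftriaxone". Table 6 carries the same item, "Allergic reaction that caused cessation of ceftriaxone", as one of six rows, and a line for the total number of adverse reactions follows the table.

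The Summary study protocol gives the regimen as "ceftriaxone at a dose of 2 g, given every 24 h intravenously for 4 days".

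The other safety route is the reporting of serious events. In hospital, "All SAEs and SUSARs during the hospital stay are recorded in case record forms by the treating physician"; later, "SAEs and SUSARs occurring after discharge are recorded during the follow-up interview at 3 months". Table 5 lays SAEs out by seriousness criterion, for example "Life-threatening event".

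Under Safety outcomes, complications, SAEs and SUSARs "per patient will be tabulated according to treatment group, and analyzed using the chi-squared test".

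**The concern.** The allergy item counts a treatment decision made because of a reaction, not the reaction itself. It is the only such row in Table 6. The other five (C. difficile diarrhea, infection with a resistant organism, phlebitis, raised liver enzymes, and oliguria or raised creatinine) count the event whatever was done about it. Adding all six into one total therefore mixes two kinds of count, and the total omits allergic reactions that did not end treatment.

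At stake is the harm side of the report. Complications of treatment are a named safety outcome, and known hypersensitivity is an exclusion criterion, so the trial itself treats allergy as a relevant risk of the study drug. A reader who weighs benefit against harm would look in Table 6 for how often allergic reactions occurred, and would find only how often they led to stopping. The primary outcome, the power and the efficacy comparisons are not affected.

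**Working it through.** The plan states no figure that depends on this definition, so there is nothing to reproduce. The check sets the definition against the regimen and the other safety routes.

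**Inputs**
- Definition: allergic reaction that led to ceftriaxone being stopped (Assessment of safety outcomes; Table 6).
- Regimen: every 24 h for 4 days (Summary study protocol). The treatment-adherence definition, under the section on protocol deviations, agrees: "received ceftriaxone 2 gram each 24 hours for 4 days". That is four doses, at about 0, 24, 48 and 72 h.
- Early ends to the course that still count as per-protocol treatment include discharge, a palliative care policy and a change to another antibiotic because of infection (same section).
- SAEs and SUSARs are recorded in hospital and at the 3-month interview; Table 5 has rows for seriousness criteria only.

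**Where each kind of reaction is shown**

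| Allergic reaction | Table 6 row and total | Table 5 |
|---|---|---|
| During the course, ceftriaxone stopped because of it | Counted | If serious, by criterion only |
| During the course, ceftriaxone not stopped because of it, serious | Not counted | By criterion only |
| During the course, ceftriaxone not stopped because of it, not serious | Not counted | Not shown |
| After the fourth dose, or after a course already ended for another reason, serious | Not counted | By criterion only |
| The same, not serious | Not counted | Not shown |

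SUSARs are unlikely to fill the gap. They are by name unexpected, whereas the plan lists allergy among the complications it anticipates.

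**Direction**

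Let f be the share of allergic reactions that did not cause cessation. Then

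counted = true × (1 − f).

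Since f lies between 0 and 1, the count equals the true number only if f = 0 and can never exceed it.

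**Size**

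The document gives neither the allergy rate nor f, so the loss cannot be computed. The following only shows scale, and both the 2% rate and the values of f are assumptions. Of 2,550 patients randomized 1:1, about 1,275 are in the ceftriaxone arm. A true rate of 2% gives 1,275 × 0.02 = 25.5 reactions. The row would then show:
- f = 10%: 25.5 × 0.90 = about 23
- f = 25%: 25.5 × 0.75 = about 19
- f = 50%: 25.5 × 0.50 = about 13

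**Comparison between arms**

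Patients in the standard-care arm are not allocated any preventive ceftriaxone that could be stopped. Apart from crossovers, the row is near zero there by construction. Its chi-squared P value therefore reflects the definition at least as much as any difference in allergic reactions.

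**The case against.** The strongest reply is that the row says exactly what it counts. Nothing in the SAP article calls it an allergy rate, and limiting a complication to events that ended treatment is a legitimate, pre-specified threshold. This stands for the row: it is not mislabelled. It does not stand for the total, which is presented as the number of adverse reactions and gives no sign that allergy enters only in part.

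Second, serious reactions are not lost. A reader might infer that a late anaphylaxis would vanish from the safety results. The document does not support that: it would be recorded as an SAE in hospital or at 3 months, and would be tabulated and tested by arm. Nothing prevents a narrative description either. What the planned tables lack is its identification as allergy. The reactions with no place in any table are the non-serious ones that did not stop treatment, which carry the least weight in judging harm.

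Third, definitions and collection of adverse events may be fuller in the protocol, which is not shown. That is possible. But the table shells are fixed in this document, and they have no place for other allergic reactions even if those were collected.

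Fourth, recruitment had finished by 23 March 2014, and the CRF item may have been worded as quoted. A complete row for any allergic reaction may then be impossible to fill. Discharge letters would not settle this: the document mentions them only for last-observation scoring of patients lost to follow-up and for review of cause of death. This objection stands, and it limits the remedy.

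**Conclusion.** The point holds as a gap in safety reporting. The cessation condition leaves out allergic reactions that began after the last dose or that did not lead to stopping, both from the allergy row and from the Table 6 total. Serious ones remain in Table 5, without being recognizable as allergy.

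The undercount can go only one way, and this follows from the definition alone. Its size is unknown and may be small. A reader might be tempted to put a percentage on it by assuming that reactions start evenly over some period after the first dose. The document gives no onset times, so any such figure would only restate the chosen period. Nor does the text support a claim that ceftriaxone allergy will be materially understated, or that any conclusion of the trial would change.

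The conclusion assumes that Tables 5 and 6 are used as drafted and that no further allergy listing is planned elsewhere.

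**What to change.** In Assessment of safety outcomes and Table 6, before the code is broken:

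1. Keep the present row, titled as ceftriaxone stopped for allergic reaction.
2. Add a row by arm for allergic reactions, with anaphylaxis shown separately. Identify them from the SAE and SUSAR reports already held, plus any CRF complication entries that recorded reactions not leading to cessation.
3. Include these in the Table 6 total, and count once any reaction that falls in both rows.
4. If the CRF captured only cessation events, state under the table that non-serious reactions not leading to cessation were not captured. Do not report either the row or the total as the drug's allergy rate.

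The cost is one added row with a sub-row, one footnote, and a modest extra review of safety reports already held. The reported count in the ceftriaxone arm may be slightly higher. The change affects only counting and labelling, and implies no rule on when treatment is stopped.
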